### Who will take informed consent? {26a}

Parents/legal guardians of eligible adolescents have to confirm their consent via a pre-scripted email sent to the research group. The lead investigator (GM) will accept the emails. Links to the study questionnaires are only sent after receiving this email. Adolescents will tick a box at the beginning of the pre-test questionnaires asking for their consent.

### Additional consent provisions for collection and use of participant data and biological specimens {26b}

This is not applicable as this is not an ancillary study.

## Interventions

### Explanation for the choice of comparators {6b}

This is an early stage first analysis of the developed game. We are interested in the effects of the whole game, not its specific components. Therefore, we use a puzzle game without psychoeducational components as comparator to control for time spent online with a game. Using another game instead of no game at all helps consider expectation bias and potential lack of interest to continue the study in a control group.

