## Intervention description {11a}

### Experimental intervention

An iER adventure game was/is currently being designed and developed using both scientific research and co-development workshops with children of the targeted age group to assure that the game has both learning and fun components. It is a single-player role-play/adventure game with 3 levels and a hub world (connecting the levels). It is played from a top-down perspective and created with the commercially available RPG Maker MV. The game is played on a phone or a browser. The game software will allow us to collect data on how the game was played, i.e. which options the participants chose and different time points (e.g. start time, end time). All conversations in the game will be presented in text through conversation windows. Total playtime depends on the player, as the explorative nature of the game allows more or less exploring, but to complete the game, approximately 3 h will be necessary. For the duration of the study, the game will be freely accessible (but will ask for a participant code to enter) via https://dot-game.picapipe.dev/.

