### The control intervention

The control group will receive a free-to-play arcade browser puzzle game with no psychoeducational content. The game requires the player to clear a field of multicoloured bubbles by trying to group same-coloured bubbles into groups of three or more. Single coloured bubbles are used one by one to shoot at the field and change its configuration. The game is won when no bubble remains and can then be started again. It is freely available under https://www.squidbyte.com/games_third/bubbleshooter/bubble-shooter/.

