### Participant timeline {13}

This RCT adopts a pre-post-test strategy with the between-participant factor “group” and the within-participant factor “time”. Assessment will include pre-tests (questionnaires; day 1), intervention (playing the game; days 1–5), and post-tests (questionnaires and acceptability measures; days 5–10). After sending the consent forms, every participant will receive the link to the pre-test questionnaires via email. They take approximately  30 minutes to complete. At the end of these questionnaires, participants will be randomly assigned to either experimental or control group and receive the appropriate link for the corresponding game. Additionally, participants are asked to provide a unique identifying code consisting of the first letter of their own first name, the first letter of their mother’s first name, the first letter of their father’s first name, and the day of their birthday. They will use this code in the subsequent parts of the study to allow to link the parts anonymously. The link for the games can be opened as soon as they receive it and accessed with the unique identifying code that they used in the pre-test questionnaires already. Participants are asked to play the game for as long as they want but with the aim to finish it. After that, the participants have 5 days to play the game. They receive the link for post-test questionnaires 5 days after the first link was sent. The post-test questionnaires will take approximately 30 minutes to complete. After 2 days, a generalised reminder is sent to each participant via email to remind them to finish the study if they have not done so already.

The iER AG allows for great variability in playtime, but no matter how long each player takes to finish the game, everyone will have the same amount of iER interactions. As long as they play the game to the end, playtime has no influence on the psychoeducational component but only on the explorative “fun” part of the game. In general, we expect the average playtime to be approximately 3 h in total. The control group will get instructions to play the game as much as they want for the next days. They will receive the final questionnaires 5 days after they started the study. For an overview of the study design, see Fig. 1.

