*Gaming experience and preference*. Willingness to engage and hence outcomes might be influenced by gaming experience and gaming preference [47]. The style of the game in this study might remind some participants of games they already played as it is a common style in especially older AGs and some participants might have more experience. We will cover gaming experience with four questions specific to the current study: [1] Do you like videogames (answers are given on a 4-point scale: yes; rather yes, rather no, no)? [2] How much do you play per week (not at all (0 h); little (0–2 h); medium (3–5 h), a lot (more than 5 h))? [3] Have you ever played an adventure game (yes; no)? [4] If yes, what was the name (open question)?.

*Sociodemographic questions and questions to assess potential contamination*. Sex and age will be asked at the beginning of the questionnaires. After the intervention, participants will be shown a screenshot of the intervention game and asked if they have seen this game before. As we cannot gather data of the control game, we will additionally ask for how long the game was played approximately (0-30 min; 30 min–1 h; 1–2 h; more than 2 h). For an overview of the measures, see Table 4.

**Table 4 Tab4:** Measures used in the study

Measure	Assessment tool	Timepoint		
		Pre-test	In-game	Post-test
IER	Vignettes with hypothetical iER situations	x		x
ER	Emotion Regulation of Others and Self scale (EROS; 42)	x		x
Emotional competence	Emotional Skills and Competence Questionnaire (ESCQ; 44)	x		x
IER strategies	In-game option patterns		x	
Gaming experience	Self-developed questions	x		
Gender	Inventar zur Erfassung des Geschlechtsrollen-Selbstkonzepts im Jugendalter (GRI-JUG; 46)	x		
Acceptability	Game User Experience Satisfaction scale (GUESS-18; 45). In-game measures (drop-outs, time)		x	x

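### The comparator is said to control for time spent with a game, but the design does not ensure equal time and the playtime item cannot confirm it near the expected 3 h

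*Protocol article*

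**What the plan says.** The section on the choice of comparators {6b} gives the puzzle game a specific purpose: "to control for time spent online with a game". It adds that having a game at all addresses expectation bias and loss of interest in the control group, and that interest lies in the game as a whole, not its components.

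On the experimental game, the intervention description states that "to complete the game, approximately 3 h will be necessary", and the participant timeline {13} repeats that "we expect the average playtime to be approximately 3 h in total". The play instruction there reads: "Participants are asked to play the game for as long as they want but with the aim to finish it".

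On the control game, the intervention description says: "The game is won when no bubble remains and can then be started again". The timeline gives this arm its own sentence: "The control group will get instructions to play the game as much as they want for the next days".

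On measurement, the experimental game's software records choices and time points such as start and end. The control game yields no data, so, under Secondary outcomes, "we will additionally ask for how long the game was played approximately". The four answers are up to 30 min, 30 min to 1 h, 1 to 2 h, and above 2 h.

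On analysis, the primary analysis section compares the proportions improved by chi-square test. A logistic regression follows, with group, language, total playtime and the interval from last play to post-test as independent variables.

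**The concern.** A comparator controls for time with a game only if the design makes time similar in the two arms, or if the data can show that it was. Here one arm has a finite story of about 3 h and a request to finish it. The other has an open-ended puzzle and no target. The only playtime information from controls is a coarse self-report that stops resolving below the duration expected in the other arm.

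The stake is how a between-arm difference is read. If the adventure-game arm does better and also spent longer on its game, the stated rationale would lead a reader to believe that time had been held constant when it had not. A second, smaller stake is the regression: total playtime comes from a log in one arm and can come only from a banded self-report in the other, and the article does not say how the two are put on one scale.

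**Working it through.** **1. The plan's own figure.** The sample size was checked first, to see whether it is touched. Inputs from Sample size {14}: 30% against 10% improved, 80% power, significance level 0.05 (taken as two-sided). With a pooled mean proportion of 0.20:

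n per arm = [1.960·√(2·0.20·0.80) + 0.842·√(0.30·0.70 + 0.10·0.90)]² / (0.30 − 0.10)² = [1.109 + 0.461]² / 0.04 ≈ 61.6, so 62.

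This matches the stated 62 (power at 62 per arm is 80.3%). Allowing for 30% drop-out gives 124 / 0.70 = 177.1, or 178 when rounded, against the stated 180. Playtime enters neither this calculation nor the chi-square test, so nothing here changes.

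**2. What sets exposure time in each arm.**

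| | Experimental | Control |
|---|---|---|
| Natural end point | Yes, three levels and a story | None fixed; restartable after a win |
| Time to reach it | About 3 h | Not stated |
| Instruction | As long as wanted, aiming to finish | As much as wanted |
| Minimum or target time | None beyond completion | None |
| Window | 5 days | 5 days |

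Only the last row is common to both arms by design. Equal playtime could occur, but nothing in the plan brings it about.

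**3. What the playtime item can show.** The open band starts at 2 h and the expected experimental playtime is about 3 h, so the band opens 3 − 2 = 1 h below it.

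- A control who played less than 2 h falls in one of the three lower bands. A shortfall of that kind would be visible.
- A control who played 2.1 h and one who played 6 h give the same answer.
- Logged experimental times can be grouped into the same four bands. A child who finishes in about 3 h lands in the open band. If most of both arms land there, the item cannot say whether the times were similar, shorter in controls by up to about 1 h, or longer.

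**4. Illustration only.** The article gives no expected control playtime. If controls played between 0.5 and 2 h (an assumption), the gap to 3 h would run from 3 − 2 = 1 h to 3 − 0.5 = 2.5 h per child. Playtimes below 2 h are the part of the range that the existing bands would detect.

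**5. The regression.** Total playtime arises after randomisation, and the design lets its distribution differ by arm. A group coefficient adjusted for it therefore compares arms at equal playtime. That is a different question from the effect of being assigned the game. It also depends on the unstated rule that combines minutes from a log with bands from recall.

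**The case against.** Several counter-arguments have force.

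- **Checkability.** A reader might infer that the time claim cannot be checked at all, or that the two measurements cannot be compared. Neither follows. The bands would expose a control shortfall below 2 h, and logged times can be grouped into the same bands. What remains is the lack of resolution above 2 h and the residual difference between log and recall.
- **Who is asked.** The article does not clearly limit the playtime question to controls. It follows an item put to participants in general, so part of the remedy may already be intended.
- **The instructions.** Both arms may play as long as they like within the same 5 days. The sentence about aiming to finish refers to participants generally and could be read as covering both. Even so, clearing one field of bubbles is not equivalent to completing a story of about 3 h, so the broader reading does not equalise time.
- **The target of inference.** A reader might infer that the comparator was meant to isolate psychoeducational content from duration. The comparator section says that the whole game is of interest, and its length is part of that whole. The article also gives no reason why more time on a bubble puzzle would raise the number of strategies recalled. This lowers the stakes, but the same section still makes the claim about time, and the rest of the design does not support it.
- **Other purposes.** The handling of expectation bias and of loss of interest in controls is untouched.

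**Conclusion.** The point stands as an inconsistency between a stated design property and the design itself. The comparator section claims control of time; the play instructions and the nature of the two games do not ensure it; and the playtime item can reveal a shortfall below 2 h but cannot confirm comparability around 3 h.

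The size that the article itself supports is the 1 h between the start of the open band and the expected playtime. The gap of 1 to 2.5 h per child rests on an assumed control playtime and should not be reported as a finding. A reader might also infer that the arms will in fact differ in exposure. The article does not establish that, only that the design leaves it open.

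The validity of the primary test, the sample size and the power are unaffected. The consequence is for interpretation and for the meaning of total playtime in the secondary regression. The article presents that regression as exploring influences, not as the main estimate, so the caution concerns how its group coefficient is read.

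**What to change.** 1. Reconcile the comparator rationale {6b} with the play instructions in the participant timeline {13}. One way is to state that the comparator controls for being given an online game to play, and not for equal time.
2. State that the same self-reported playtime question is asked in both arms, with bands that continue past 3 h. This also gives total playtime a common scale in the regression. The experimental log can be kept as additional information.
3. Report the distribution of that item by arm, descriptively.
4. State in the primary analysis section that a group effect adjusted for total playtime is not the treatment effect, because playtime is determined after randomisation.

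The cost is one reworded survey item, a few sentences of text and a slightly weaker stated rationale. Trial status places the study before recruitment, which is the time to do this: the control game leaves no log and participation is anonymous, so finer playtime data would be hard to recover later.

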## Intervention description {11a}

### Experimental intervention

An iER adventure game was/is currently being designed and developed using both scientific research and co-development workshops with children of the targeted age group to assure that the game has both learning and fun components. It is a single-player role-play/adventure game with 3 levels and a hub world (connecting the levels). It is played from a top-down perspective and created with the commercially available RPG Maker MV. The game is played on a phone or a browser. The game software will allow us to collect data on how the game was played, i.e. which options the participants chose and different time points (e.g. start time, end time). All conversations in the game will be presented in text through conversation windows. Total playtime depends on the player, as the explorative nature of the game allows more or less exploring, but to complete the game, approximately 3 h will be necessary. For the duration of the study, the game will be freely accessible (but will ask for a participant code to enter) via https://dot-game.picapipe.dev/.

#### Storyline

The setting of the game is in a school, the playable character (PC) is a pupil. The game starts with a normal school day for the PC to familiarise the player with the style of the game. After that day, the PC stays home for a day because they are sick. They receive strange, rude text messages during this time. When they return to school, everything has changed. Pupils are very aggressive, fighting and arguing everywhere. Suddenly, there is an explosion, and everyone is gone. The school is dark and dusty. The PC does not know what happened. While exploring, the PC finds four other remaining pupils and forms a group of friends with them. Together, they pass through three portals that can be found in the school and that lead to different fantasy worlds. In these fantasy worlds, the group needs to find their way back and save the pupils that have vanished. Between levels, the group meets a mysterious goldfish who turns out to be the guardian animal of the school. The goldfish helps them understand the interpersonal conflicts, the reason for the catastrophe, and their role in resolving it. After completing each fantasy world, the school is restored a little bit more. After completing all worlds (levels), the school is fully restored. Nobody except the group remembers what happened.

#### Psychoeducational component

The game teaches and trains iER through various techniques:

1. Interaction with non-playable characters (NPCs): The group encounters a variety of NPCs on their way who show various emotions. The player needs to interact with these NPCs appropriately and use adaptive strategies to help them deal with their emotions. Emotions include fear, anger, disappointment, and sadness.

2. Interactions within the group: The player receives information about group members during conversations and gameplay that need to be remembered and addressed appropriately. This can for example be information about fears (someone is scared of the dark).

3. Happy, the goldfish: The player meets the goldfish after each level. It serves to help internalise and repeat psychoeducational content learned during the level.

#### Feedback

The teaching of correct iER strategies is mainly achieved by varying feedback. Ultimately, the player cannot proceed and finish the game when using the wrong (i.e. maladaptive) strategies. Specifically, there will be:
Audio and visual feedback: sounds and pictures (similar to emojis, e.g. heart-shaped) over the receiving agent’s head will indicate if a strategy was successful.Feedback from receiving agents: Receiving agents will clarify if a strategy was good (e.g. “Thank you for listening to me without interrupting!”) or maladaptive in this situation (e.g. “That just made me feel worse.”).Rewards and achievements: After some successful interactions, the player gets rewarded with items (received as gifts from the receiving agent). Items can be sold for in-game money or are needed in further interactions or levels to proceed in the game.

### The control intervention

The control group will receive a free-to-play arcade browser puzzle game with no psychoeducational content. The game requires the player to clear a field of multicoloured bubbles by trying to group same-coloured bubbles into groups of three or more. Single coloured bubbles are used one by one to shoot at the field and change its configuration. The game is won when no bubble remains and can then be started again. It is freely available under https://www.squidbyte.com/games_third/bubbleshooter/bubble-shooter/.

### Criteria for discontinuing or modifying allocated interventions {11b}

Neither the measurements nor the gameplay is expected to result in any significant harmful side-effects, as the game has no graphic depiction of violence and none of our measures are invasive. Thus, we do not expect that we need to modify the interventions during the duration of the study. As the study is completely automated and anonymous, individual participants cannot be identified.

### Strategies to improve adherence to interventions {11c}

This study is executed online. Researchers have little influence after participants begin the study, but deviation from the protocol is unlikely due to automated online processes.

### Relevant concomitant care permitted or prohibited during the trial {11d}

There will be careful consideration to avoid active recruitment of participants that have already participated in co-development workshops e.g. by not advertising the study in schools that have recently been or currently are part of another study or workshop with our research group. Schools that participated more than a year ago pose no problem as pupils from classes that participated would be excluded due to the narrow age span of the study.

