### Limitations and rationale

Overall, there are some gaps and limitations in the existing literature that lead to the idea and necessity of this study, most importantly the lesser focus of research on iER and the lack of serious games for a general population of early adolescents.

Concluding, iER skills can influence the successful establishment and maintenance of friendships and relationships of early adolescents, yet literature on iER in that age group is scarce. Research thus far has not sufficiently understood the concept of iER and the potential of training it targeting adolescents on a broad scale in the general public. We aim to fill this gap by developing a serious game that helps early adolescents express their strategies in situations requiring iER skills. The development of the game included an extensive literature search on iER, and in-game strategy-options were generated by using original material from Niven, Totterdell [4] study, which the authors kindly provided. Co-development workshops with children of the relevant age group helped with including ideas and remarks from the target group. The interdisciplinary research team included a diverse range of professions such as psychologists, computer scientists, and playwrights.

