### Eligibility criteria {10}

Eligible participants will be early adolescents between 10 and 14 years. Furthermore, participants have to be able to read and understand German or English as the game can be played in these two languages. They must also provide written parental consent and be willing to participate in the study by filling out questionnaires at two time-points (pre- and post-test) and playing a web-based game in between. The game targets iER in the general population of early adolescents. Hence there will be no restrictions in terms of learning difficulties or mental health problems (see Table 2).

**Table 2 Tab2:** Eligibility criteria

	Inclusion criteria	
1.	Between 10 and 14 years old	
2.	Willing and able to provide written parental consent	
3.	Willing and able to participate in filling out pre- and post-test online questionnaires and playing a web-based game	
4.	Able to read and understand German or English	
5.	Access to a device with internet (computer, mobile phone, tablet)	

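### The 10–14 age range does not screen out pupils from co-development workshops held more than a year ago, although section {11d} relies on it to do so

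*Protocol article*

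**What the plan says.** The section on concomitant care {11d} sets out how the trial avoids enrolling children who helped to develop the game. It first says that such children will not be actively recruited, giving as an example that schools with recent or current involvement will not be targeted with advertising. It then clears the remaining schools: "Schools that participated more than a year ago pose no problem", because "pupils from classes that participated would be excluded due to the narrow age span of the study".

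The age criterion is in Eligibility criteria {10}: "Eligible participants will be early adolescents between 10 and 14 years", repeated in Table 2 as "Between 10 and 14 years old". Table 2 lists five inclusion criteria. None concerns workshop participation or earlier play.

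Two sections describe the workshop children. Limitations and rationale says "Co-development workshops with children of the relevant age group helped with including ideas and remarks from the target group", and Experimental intervention refers to "co-development workshops with children of the targeted age group".

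The question on exposure is in Secondary outcomes, under the sociodemographic and contamination items: "After the intervention, participants will be shown a screenshot of the intervention game and asked if they have seen this game before".

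**The concern.** The age range is offered as the reason why one group of previously exposed children needs no further check. If the range does not remove them, the safeguard is not there, and following the protocol as written lets them in.

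At stake is the contrast that the trial measures. The primary outcome is whether a participant can name more helpful strategies after the intervention than before. A child who met the game's content at a workshop may have less left to learn from it and, if allocated to the control game, may already know part of what the experimental arm is taught. Either would tend to pull the two arms together.

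**Working it through.** The contested sentence carries no figure, so there is nothing of the plan's own to reproduce. The check is age arithmetic on the protocol's own criteria.

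**Inputs**
- Eligible ages: 10 to 14 (Eligibility criteria {10}, Table 2).
- Age at workshop: the same age group (Limitations and rationale; Experimental intervention).
- Time since workshop: more than one year (section {11d}).

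**Step 1: by year of age.** A pupil aged *a* at the workshop is still eligible *t* years later if *a* + *t* ≤ 14.

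| Age at workshop | After 1 year | After 2 | After 3 | After 4 | After 5 |
|---|---|---|---|---|---|
| 10 | eligible | eligible | eligible | eligible | out |
| 11 | eligible | eligible | eligible | out | out |
| 12 | eligible | eligible | out | out | out |
| 13 | eligible | out | out | out | out |
| 14 | out | out | out | out | out |

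At the protocol's one-year mark, only the 14-year-olds have left.

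**Step 2: as a share.** The protocol does not give the age distribution of the workshop children. Assuming an even spread over an eligible span of *S* years, the share still eligible is (*S* − *t*)/*S*.
- Upper limit read as the 15th birthday, *S* = 5: (5 − 1)/5 = 80% after one year, (5 − 2)/5 = 60% after two, 40% after three, 20% after four, 0% after five.
- Upper limit read as the 14th birthday, *S* = 4: (4 − 1)/4 = 75%, (4 − 2)/4 = 50%, 25%, then 0% after four. On this reading pupils aged 13 at the workshop also drop out after a year.

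Complete ageing-out therefore takes about 4 to 5 years, not one.

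**Step 3: do the other measures cover these pupils?**
- *Advertising.* The restriction applies to schools with recent or current involvement. Section {11d} itself releases schools involved more than a year ago. Recruitment {15} also uses social media, which a school-level rule does not reach, and it expects schools to join because they have worked with the team before.
- *Eligibility.* Table 2 contains nothing on the subject.
- *Pre-test.* Table 4 lists no prior-exposure item. The gaming-experience questions ask whether the child has ever played an adventure game and what it was called. An answer might happen to name this game, but the item is not directed at that and is not tied to eligibility.
- *Post-test screenshot.* By then the experimental arm has been sent to the game, so a yes in that arm cannot separate earlier exposure from the trial itself. In the control arm a yes shows contact with the game at some time. The item also asks about seeing the game, not about attending a workshop.

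**The case against.** Several points on the other side have force.

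- **There is a first line of defence.** Section {11d} does restrict active recruitment in recently or currently involved schools, and gives this only as an example. This stands, and it narrows the problem to pupils involved more than a year ago and those who arrive by other routes. It does not rescue the sentence about the age span, which is the only reason given for clearing that remaining group.
- **The workshop ages and dates are unknown.** If the classes were mainly 13 to 14 years old, or the workshops several years old, fewer pupils would remain eligible. This also stands. The percentages are conditional, while the contradiction at the protocol's one-year mark is not.
- **The post-test timing protects blinding.** Showing the adventure game before randomisation could let a participant later sent to a bubble game infer the allocation, against sections {16a} and {17a}. This is correct, and it means that the screenshot should not be moved forward. A text question does not carry the same risk if it is worded neutrally.
- **Exposure may have been slight.** Workshop children contributed ideas. The documents do not say that they were trained or that they played the current game. The vignette task is open-ended with no stated maximum, so a ceiling is an assumption.

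Two stronger readings are tempting but are not supported. A reader might infer that the plan breaks the randomised comparison by removing participants on a post-test answer that is informative mainly in controls. No section says that anyone will be excluded on that answer; it is listed as an item to assess contamination. A reader might also put a figure on the lost effect: if a fraction *f* of participants could not gain at all, the assumed difference of 30% − 10% = 20 points would become 20(1 − *f*), or 18 points at *f* = 10% and 16 at *f* = 20%. With 180 participants those fractions mean 18 and 36 former workshop children, which nothing in the protocol supports. The share of workshop pupils still eligible is not the share of the trial sample that was exposed.

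**Conclusion.** The point holds as a false safeguard. With eligibility at 10 to 14 and workshops in the same age group, the age criterion does not exclude former workshop pupils after one year. It would need about 4 to 5 years to exclude them all. The figures of 75–80% still eligible at one year and 50–60% at two rest on an assumed even age spread and describe workshop pupils, not trial participants.

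The consequence is limited. Randomisation balances prior exposure between the arms on average, so the expected effect is some dilution and not systematic bias. Its size cannot be computed from the protocol, and the sample size calculation and primary test are not affected. The point deserves correction because section {11d} relies on the statement and the repair is very cheap.

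**What to change.** 1. Delete the sentence in section {11d} that relies on the age span.
2. Add to Table 2 an exclusion for having taken part in a co-development workshop for this game or having played it before.
3. Ask about this before randomisation, either in the online pre-test or in the parental consent email of section {26a}, and end participation there for those who answer yes. Use a neutral text question with no screenshot and no description of the game, so that blinding is preserved. Randomisation already takes place at the end of the online pre-test, so the order of events does not change.
4. Keep the post-test screenshot item, and state that it serves only to describe contamination in the control arm and is not used to exclude anyone.

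The cost is one extra question, one line in Table 2 and a few volunteers lost at entry. The check depends on self-report or a parent's report and will miss some cases.
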